**Game Changers for CC Prevention (GC-CCP).** GC-CCP draws on theories of network diffusion, cognitive consistency, and social influence, which posit that behavior change can be initiated by a few and diffused to others through modeling, advocacy, and shifts in social norms. GC-CCP uses 7 sessions to empower CC screened women to act as change agents for CC screening in their social networks. **Session 1** addresses fears and concerns related to CC risk and use of self-compassion and peer support to overcome these fears. **Session 2** focuses on decision making for sharing one's personal CC screening experience, and how to initiate disclosure and conversations about CC. **Session 3** builds self-efficacy for CC risk management so that one's own behavior (e.g., recognizing signs of CC risk and seeking CC-related health services as needed; periodic VIA screens) coincides with the behavior they encourage in others, as well as learning CC facts and myths to facilitate accurate CC screening advocacy. **Session 4** demonstrates how one's social network can serve as a tool for dissemination of CC prevention advocacy and knowledge. **Sessions 5 and 6** build CC advocacy skills: communication skills (e.g., reflective listening, paraphrasing, open ended questions), and how to start and sustain conversations about CC. Participants learn to identify alters in their network who may be prime targets for advocacy and transfer of information and norms throughout the network (e.g., well connected to other alters; are "bridges" between two distinct groups of alters). **Session 7** inspires commitment to ongoing CC advocacy through peer solidarity and support. The 2-hour, weekly sessions will be conducted in Luganda using a structured manual, and group format to facilitate: sharing of experiences to build solidarity, support, and motivation among participants; group problem solving and role playing to build skills and self-efficacy; and homework between sessions to practice new skills and generate experiences to be processed in the sessions.

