**1st degree alters:** The site coordinator will use the social network assessment within the baseline survey of each index to randomly select (using a random number table) 5 alters who know the participant's CC screening experience (or as many as there are if < 5) and ask the index if she is comfortable recruiting 3 of these alters. The index will be asked to call each selected alter at the end of their baseline interview to describe the study in the presence of the coordinator (or later in private, if she prefers), who will schedule a study visit for the alter. If an alter refuses or cannot be reached, a replacement will be randomly chosen from the original list of 5 alters.

**2nd degree alters:** The site coordinator will use the social network assessment in the month 6 survey of each 1st degree alter to randomly select 4 alters (or as many as there are if < 4) who the alter reports targeting with CC screening advocacy and thereafter was screened for CC. A similar process as described above for 1st degree alters, will be used to recruit and enroll 2nd degree alters. The coordinator will obtain verbal consent from the 2nd degree alter over the phone and the complete a brief 15-minute phone survey.

**Assessment schedule:** Surveys will be administered at baseline, month 6 and month 12 for index and 1st degree alters, and 2nd degree alters will be surveyed only once (at month 6 assessment of 1st degree alters). Participants will receive 30,000 Ush (~\$8) per assessment, except 2nd degree alters who will receive 10,000 Ush (via mobile money). To limit attrition, we will collect tracking information (phone numbers and mapped addresses), including contacts for family/friends with whom they have frequent contact. Clinic staff will help us track clients we have difficulty reaching. In the pilot, >96% of index and alters were retained at month 6.

**Measures:** Survey assessments for index and 1st degree alter participants will be interviewer-administered in Luganda using Network Canvas software, last ~ 75 minutes, and include a social network assessment. CC screening and treatment utilization will be verified with medical chart data.

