| Survey Constructs                                                                                                                   | Instrument                                                                       |
|-------------------------------------------------------------------------------------------------------------------------------------|----------------------------------------------------------------------------------|
| Primary Outcome                                                                                                              |                                                                                  |
| CC screening (VIA) and results                                                                                                      | Survey; medical chart                                                            |
| Secondary Outcomes                                                                                                           |                                                                                  |
| CC-related treatment (e.g., cryotherapy, thermal therapy; radiation); biopsy                                                        | Survey; medical chart                                                            |
| CC prevention and treatment advocacy (general)                                                                                      | 6 items; dev. In- house; alpha=.95                                               |
| CC screening advocacy with specific alter (discussed/encouraged/gave info/direct support)                                           | 4 items; dev. In-house; alpha=.87                                                |
| CC screening advocacy received from index as perceived by alter (discussed/encouraged/gave info/direct support) (alter survey only) | 4 items; dev. In-house; alpha=.86                                                |
| Potential Mediators                                                                                                          |                                                                                  |
| CC knowledge (etiology, prevention, treatment)                                                                                      | 16 items; dev. in-house; alpha=.75                                               |

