**Social network assessment:** The participant will list 10 female alters (which is adequate for structural and compositional variability) with whom they interact most. For each listed alter, we will gather information to assess *network composition* (e.g., age, relation to respondent, history of CC screening and treatment; knowledge of respondent's CC screening experience). In the index survey only, we will ask how if each alter knows each other alter to assess *network structure* (e.g., density); this section is time consuming, so given the large number of alter participants, alters will not complete this survey component. Research questions related to this section [e.g., do denser networks promote more CC screening within the network) will be addressed with index participant data. To assess CC advocacy and perceived effects, from the perspective of both the index and alter, we will ask the participants if they have engaged in CC screening advocacy (separate items for discussed, encouraged, gave info, gave direct support, and frequency) with the specific alter in the past 6 months, and any perceived resulting action (e.g., alter was screened). At follow-up, we will determine whether listed alters are the same or unique from those listed at baseline, to facilitate longitudinal analyses of alter data.

**Phone assessment of 2nd degree alters** will assess background characteristics, receipt of CC screening and treatment services, CC knowledge, receipt of CC screening advocacy from referring 1st degree alter, engagement in CC prevention advocacy (general), number of alters engaged in CC screening advocacy with, and the number of these alters perceived to have been screened for CC following this advocacy.

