Harm from CC risk disclosure or advocacy. Among the goals of the intervention sessions are to improve the participants' ability to make effective decisions regarding disclosure of their CC risk status and engaging in CC prevention discussions with members of their social network. These sessions will be designed to help participants recognize the full range of responses that they may encounter when disclosing their status or discussing CC, including the potential for recipients of such information to act with hostility, discrimination, or other negative responses. Hence, the sessions focus on decision making regarding these behaviors, and improving judgment for when such behaviors will be beneficial versus harmful, rather than encouraging all participants to disclose or advocate prevention regardless of risk for harm. These procedures cannot prevent all negative responses, but should minimize such risks. In the pilot of the intervention, no adverse events were reported in this regard.

**Inadvertent CC risk disclosure to recruited social network member:** Index participants will be asked to consider recruiting up to 3 of their network members to participate in the study survey, and 1st degree alters will be asked to recruit up to 2 of their social network members. Participants will be informed that this is not a requirement and that they should only ask people who they are comfortable with approaching to participate. These participants will be asked to consider selecting these network members from a list of 5 randomly selected network members (generated by the study) whom they report know the participant's CC screening experience/result (if there are less than 5 named members who know the participant's CC screening experience/result, then only those who do know will be selected). This procedure should limit the risk of the participant trying to recruit a network member who does not know the participant's CC screening experience/result, but participants are allowed to recruit network members who are not on the list of 5 members provided to them by the study, so it is possible. However, participants will be counseled on the risks of approaching such a network member, as someone who does not know the index participant's CC screening experience could assume the index participant has CC or CC risk given the nature of the study.

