#### *B. Types of Data.*

*Medical chart data:* We will obtain data related to cervical cancer (CC) screening and treatment services, including biopsies, received for all index and alter participants.

*Survey and social network assessment data:* The survey assessments will be administered using Network Canvas, and will collect information about participant demographics; use of CC screening and treatment services; engagement in CC prevention advocacy; CC knowledge/beliefs; self-efficacy related to use of CC-related medical services and engagement in CC prevention advocacy; sharing of personal experience related to CC screening; CC internalized and enacted stigma; social support; and relationship status and sexual

behavior. During the social network assessment portion, participants will be asked to list 10 adult females in their social network (e.g., friends, family, other community members). We will collect first name and last initial for each social network member to avoid the potential for confusing individuals who might have the same first and last initial, and to assist with linking network member data across assessments (to assess network change over time). For each social network member (alter) listed we will collect information about demographics; description of the relationship between the index participant and the individual alter; CC prevention advocacy provided to the alter by the index participant; social support provided by the alter; and the alter's expression of CC-related stigma. We will also ask for a description of how often individuals listed in the social network assessment interact with each other.

*Individual qualitative interview and focus group discussion data.* Individual qualitative interviews will be conducted with providers involved with providing CC-related services, clinic administrators, and ministry of health policy makers; these interviews will focus on the respondent's perspective of CC-related services provided at the clinic, barriers to good access to CC screening and ability to scale-up provision of CC screening, and views on how to optimize client engagement in the GC-CCP intervention. Female clients of the clinics will participate in focus group discussions to share their views on CC-related services provided at the clinic, barriers to good access to CC screening, and views on how to optimize client engagement in the GC-CCP intervention.

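### Alter-specific advocacy is asked about a list of 10 women that appears to be named afresh at each follow-up, so the women measured could differ by arm and an enrolled alter can be missing from it

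*Protocol*

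**What the plan says.** All of this is in the Protocol.

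- **List and naming rule** (D2.2.1, social network assessment): "The participant will list 10 female alters", chosen as those "with whom they interact most". For each listed woman the participant reports advocacy over the past 6 months and any action she believes followed, such as screening.
- **Timing** (D2.2.1, assessment schedule): "Surveys will be administered at baseline, month 6 and month 12 for index and" 1st degree alters. The survey includes the network assessment. An index participant completes her baseline survey before she is randomised.
- **Follow-up lists** (D2.2.1): "At follow-up, we will determine whether listed alters are the same or unique from those listed at baseline". The data safeguarding plan (Types of Data) keeps first name and last initial "to assist with linking network member data across assessments (to assess network change over time").
- **Status of the measure** (D2.2.1, survey constructs table): the secondary outcomes include "CC screening advocacy with specific alter (discussed/encouraged/gave info/direct support").
- **Training** (D.2.2, description of sessions 5 and 6): "Participants learn to identify alters in their network who may be prime targets for advocacy". The control arm is trained only after the 12-month follow-up.
- **Recruitment of 1st degree alters** (D2.2.1 and Protection Against Risk): 5 women are drawn at random from the index's network list, but "participants are allowed to recruit network members who are not on the list of 5 members provided to them by the study".

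**The concern.** An arm comparison of what women did with particular members of their network needs a set of network members that randomisation cannot alter. Here the set at follow-up depends on current contact. The intervention teaches women to look over their network, choose women to approach and keep talking to them. By month 6 those women may well be among the trained participant's most frequent contacts. Control participants have no such prompt. A difference between arms could then partly reflect who is on the list rather than how much advocacy took place.

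Analysing only women named at both waves does not repair this, because being named again happens after randomisation. Women who drop off the list have no follow-up answers at all, and no analysis plan can recover questions that were not asked.

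The second consequence concerns pairs. Nothing guarantees that an enrolled alter is on her index's follow-up list. The index's account of her advocacy with the woman whose screening is the primary outcome can therefore be missing, possibly at different rates in the two arms.

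**Working it through.** The protocol gives no figure to reproduce here. The check is a reading of the text, followed by illustrations on assumed inputs.

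**1. Is the list elicited again?** The network assessment belongs to a survey given at three waves. The follow-up list is compared with the baseline list to see which women are the same, and names are linked in order to study network change. A roster carried forward would not need that comparison. Re-elicitation is therefore the natural reading, though no sentence states it outright. Nowhere is it said that baseline names or enrolled alters are added at follow-up.

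**2. Can training affect the list?** The naming rule is amount of contact. Training on whom to approach reaches only the intervention arm before month 12. Contact can change as a result, so list membership can too.

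**3. Illustration: advocacy (all inputs assumed).** A woman advocates with 5 women, 3 of them on her baseline list of 10.
- Baseline roster: 3/10.
- One non-target replaced by a target: (3 + 1)/10 = 4/10.
- Two replaced: (3 + 2)/10 = 5/10.

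Her advocacy is the same in all three cases. Scoring as a share of 10 is my assumption; the protocol does not define how the four items are aggregated over women.

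**4. Illustration: perceived screening.** Take 15% in both arms, borrowing the control screening rate from the power paragraph. Suppose trained women replace k of 10 names, displaced at random, with women they believe were screened. List rate = ((10 − k) × 0.15 + k)/10.

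| k | List rate | Excess over 15% |
|---|---|---|
| 1 | (1.35 + 1)/10 = 23.5% | 8.5 points |
| 2 | (1.20 + 2)/10 = 32.0% | 17.0 points |
| 3 | (1.05 + 3)/10 = 40.5% | 25.5 points |

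**5. Illustration: index reports on enrolled alters.** Planned enrolment is about 440. With an assumed proportion r still on the index's follow-up list, reports exist for 440 × r, before attrition. If names are kept independently, an index with three alters keeps all three with probability r³.

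| r | Alters with an index report | All three kept |
|---|---|---|
| 0.9 | 396 | 0.73 |
| 0.8 | 352 | 0.51 |
| 0.7 | 308 | 0.34 |
| 0.5 | 220 | 0.13 |

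The documents give no turnover rate, so steps 3 to 5 show what could happen and over what range. They do not estimate the bias.

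**The case against.** The strongest reply has five parts.

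- **Re-naming is inferred.** The survey instrument is not shown, and it may carry names forward or ask separately about each enrolled alter. The pilot account in D.1 follows 360 named women, none thought to be screened at baseline, to month 6, and it reports index accuracy about enrolled alters. That suggests follow-up of baseline names. This stands as a caution, but D.1 does not say how month-6 names were obtained, and the present trial's text describes comparing lists. A reader might infer that women name whomever they like; the text does not support that, since a contact rule applies.
- **The off-list recruits prove little.** A reader might infer that such recruits were never on the network list. The list of 5 is drawn from the list of 10, so a woman outside the 5 may still be one of the 10. The objection is right. What remains is that nothing requires her to be listed, at baseline or later.
- **No denominator is fixed, and perceived screening is not among the listed outcomes.** Both are correct. Scoring can properly be left to an analysis plan, but which women are asked about cannot be settled after collection.
- **Other measures cover the ground.** The alter's own report of advocacy received covers enrolled pairs whether or not the index names her, and the mediators named under Aim 3 do not include the index's alter-specific report. This limits the damage considerably. It does not help listed women who are not enrolled, nor replace the index's side of the pair.
- **A fixed roster misses real advocacy with new contacts.** True, so new names should still be collected, separately.

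**Conclusion.** The point holds as a limited weakness in data collection. As written, the protocol implies a fresh list at each wave with no names carried forward. The arm comparison of advocacy with specific alters, and of perceived screening, could therefore be biased by who is listed, and index reports on some enrolled alters could be missing. The size is unknown. The conclusion rests on two assumptions: that the follow-up list really is elicited anew, and that training shifts whom women have most contact with.

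A reader might go further and conclude that the effect on these measures will be inflated, or that the trial's main result is at risk. The documents support neither. No turnover figure exists from which to show inflation. The primary outcome is taken from enrolled alters' own charts and surveys, and the general advocacy scale and the alter-reported measure do not use the list. This is an inexpensive improvement worth making, not a threat to the main conclusion.

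**What to change.** At months 6 and 12, pre-load into the survey:

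- every enrolled alter of that index (up to 3), whether or not she was listed at baseline;
- the women listed at baseline.

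Ask the alter-specific advocacy and perceived-screening items about these fixed names in both arms, and base the arm comparison of those measures on this roster. For index participants the baseline list predates randomisation, so arm cannot have shaped it. Record newly named women separately and without a cap. They are still needed for network change and, in the month-6 survey of 1st degree alters, as the frame for selecting 2nd degree alters. If the instrument already does this, a sentence in the network assessment paragraph saying so is enough.

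**Cost.** Survey programming, using the names already kept for linking, plus time in an interview of about 75 minutes. The extra load is the number of baseline women not named again plus any enrolled alter not otherwise listed. Each needs about six questions: four advocacy items, frequency and perceived action. Two dropped names would add about 2 × 6 = 12 questions. If time is short, carrying forward the enrolled alters alone is the minimum, at most 3 × 6 = 18 questions. The change needs to be in place before month-6 surveys, since answers not asked then are lost.

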## Statistical Analysis

**Power:** Assuming 220 1st degree alters per arm enroll, 10% attrition (month 6 retention in pilot was 96%; we have retained 90-94% over 12 months in past studies in Uganda), ICC=.01-.05 range to control for clustering within the alters of each index participant, and a 15% CC screening rate in control alters (based on pilot data): the effective sample size will be 200 (ICC=.05) or 216 (ICC=.01) per arm. If ICC=.01, we will be able to detect a small effect size (11 percentage point difference) in alter CC screening at month 12 (80% power; alpha = .05). If ICC=.05, the detectable effect size is 12 percentage point difference (or odds ratio of 2.0).

**Aim 1:** *Assess effects of GC-CCP on alter CC screening.* We will use an intent-to-treat approach. In addition to comparing the arms at baseline and months 6 and 12, we will apply logistic generalized mixed models to our repeated-measures data to examine intervention effects, using a time by arm interaction to assess differences between the arms over time. We will account for correlation among participants in the same intervention group, and among alters referred by the same index, by adjusting standard errors for statistical inference tests with a sandwich estimator. We will use imputation for item nonresponse and attrition weights to account for non-random dropouts using logistic regression. We will control for and examine interaction effects with index (e.g., age), alter (e.g., knowledge of index's CC screening), and intervention (sessions completed) variables.

**Aim 2:** The analysis for this aim is described in the Preparation and Sustainment phases.

**Aim 3:** *Examine mediators and moderators of the intervention effects on alter CC screening, and index and alter engagement in CC prevention advocacy.* Potential mediators consist of intervention mechanisms (sharing of CC screening experience, CC knowledge, CC risk management, CC prevention advocacy self-efficacy), while potential moderators include age, history of CC treatment, and network characteristics (e.g., % of alters who are trustworthy). We will explore interactions between a moderator and study arm to examine if the variable moderates the intervention effects. If categorical moderators are significant, we will conduct post-hoc simple main effects t-tests with Bonferroni corrections. For continuous moderators, we will graph significant interactions at low and high levels of each score ( $\pm 1$  SD) and conduct post-hoc simple main effects t-tests with Bonferroni correction by comparing differences between discrete points on the regression lines. To test for mediation, we will run regression models where: (a) the outcome is CC screening measured at month 12 and predictors are intervention indicator, a potential mediator measured at month 6, and covariates, if any; and (b) the outcome is the same potential mediator measured at month 6 and predictors are the intervention indicator and covariates, if any. We will apply a bootstrapping approach to the results from those two models to test whether mediators account for effects, using SAS Proc Causalmed.

**Aim 4.** *Evaluate the cost and cost-effectiveness of implementing GC-CCP to increase CC screening and early-stage treatment.* We will compare GC-CCP vs. enhanced usual care on the marginal cost of increasing alter CC screening. Following standard convention, we will define the incremental cost-effectiveness ratio (ICER) as the difference in per-capita cost of the intervention versus control group divided by the difference in their average effectiveness:  $ICER = \frac{\mu_{C2} - \mu_{C1}}{\delta_{e2} - \delta_{e1}}$  ( $\mu_{C2}$  = mean per-capita cost of GC-CCP,  $\mu_{C1}$  = mean per-capita cost of usual care,  $\delta_{e2}$  = % of alters who get screened in GC-CCP,  $\delta_{e1}$  = % of alters who get screened in enhanced usual care). We will estimate confidence intervals with bootstrap methods. We will examine economic costs from a societal perspective, incorporating estimates of the frequency and duration of time spent by individuals engaging in receipt of services, as well as transportation costs and forgone employment as relevant. We will use a micro-costing approach, time-driven activity based costing (TDABC), to track all costs associated with implementing GC-CCP and enhanced usual care as estimated from data collected by the sites and study team. The cost per resource will be calculated by multiplying the quantity used by unit cost; total cost will be derived by summing individual costs. Capital costs will be annualized using a discount rate of 3% with an assumed lifespan of 30 (buildings) and 10 (furniture) years. Facilitators will record time spent on the sessions, identifying each activity (e.g., training, preparation, in-session) and session-related materials (e.g., consumable materials). Unit costs for labor will be characterized as capacity cost rates, as described in standard TDABC methodology. Intervention development (training) and ongoing costs will be differentiated; ongoing costs will be tracked to determine cost efficiencies over time, and we will differentiate fixed from variable intervention costs to assess the marginal cost of providing care to additional clients.

